### Interim analyses {21b}

Interim analyses will be conducted every 6 months. The trial may be stopped early for ethical reasons under three circumstances: if there is evidence suggesting that the intervention is harming participant safety. The final decision to terminate the trial will be made by the principal investigator and the study sponsor.

### Methods for additional analyses (e.g., subgroup analyses) {20b}

Subgroup analyses will be performed to examine differences in outcomes across various participant characteristics, such as age, gender, and baseline HCV status. Adjusted analyses will account for potential confounders and covariates, such as socioeconomic status, healthcare access, and injecting network size.

To address specific hypotheses, LMMs and generalized linear mixed models (GLMMs) will be employed. LMMs will be used to assess continuous outcomes, such as interpersonal factors and partner involvement levels, with repeated measures for each participant within dyads. GLMMs will be used to evaluate binary outcomes, such as HCV treatment initiation, incorporating random intercepts to account for clustering within dyads. Exploratory analyses will include mediation and moderation analyses to investigate the mechanisms through which the intervention affects outcomes and to identify factors that may influence the strength or direction of these effects.

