**Methods:**

The You’re Empowered for Treatment Initiation (YETI) Partner trial is a single-site randomized controlled trial evaluating the efficacy of a two-session behavioral intervention that engages injecting partners as peer navigators for HCV treatment. We aim to recruit 250 PWID and their primary injecting partners in San Francisco, California, randomizing them 1:1 to either a control or intervention group. The primary outcome is the initiation of HCV treatment, with secondary outcomes including treatment completion and sustained virologic response 12 weeks post-treatment. Data will be collected through questionnaires and electronic health records and analyzed using intention-to-treat and mixed-effects models.

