Given the randomized design, the primary comparison will include the cumulative incidence and risk ratios with 95% CI for HCV treatment initiation by Index participants at 6 months post-enrollment and across the entire follow-up period by randomization group. We will use a survival framework that acknowledges loss to follow-up with at-risk time beginning at study enrollment and censoring at the date of the final attended follow-up visit. The event of interest is HCV treatment initiation using a known or self-reported date of HCV treatment initiation.

Secondary analyses will include comparisons of other treatment completion and SVR12 by randomization group, with subgroup analyses for a stratum of Index ≤ 30 years of age, gender, race, and ethnicity.

While all Index participants will be living with untreated HCV at the time of study enrollment, some injecting partners will also have untreated HCV infection and may benefit from intervention involvement. Exploratory analyses will measure differences in the probability of initiating HCV treatment for HCV-infected partners by randomized group.

An exploratory linear mixed model (LMM) will assess the putative mechanisms of action by which changes in partner support and interpersonal factors (over time and by group) impact HCV treatment initiation.

Additional secondary exploratory analyses with intact dyads where both partners have data on the same independent variables will enable the investigation of partnership-based research questions that explore how relationship dynamics affect behavior change in partnerships. Therefore, we will extend the mixed models described above to include actor and partner effects for the continuous partner support variables. This technique illuminates the effects that partners in injecting partnerships can have on both their own and their partner’s behavior. Estimation of separate actor and partner effects will enable us to use contrasts to test whether partner effects are greater in magnitude than actor effects. α will be set at 0.05 for these exploratory analyses.

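### The dyad random intercept named for binary outcomes cannot be estimated for Index-only outcomes, where each dyad supplies one yes/no result

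*Protocol article*

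**What the plan says.** The section on additional analyses {20b} opens its modelling paragraph with "To address specific hypotheses, LMMs and generalized linear mixed models (GLMMs) will be employed" and continues: "GLMMs will be used to evaluate binary outcomes, such as HCV treatment initiation, incorporating random intercepts to account for clustering within dyads". Initiation, the primary outcome, is the only binary example given. No link function or analysis set is stated, and the hypotheses served are not named. The only labelled hypotheses in the article, H1a and H1b under Objectives {7}, both concern initiation.

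The statistical methods section {20a} sets the primary analysis differently, at 6 months and over the whole follow-up: "cumulative incidence and risk ratios with 95% CI for HCV treatment initiation by Index participants". It adds: "We will use a survival framework that acknowledges loss to follow-up with at-risk time beginning at study enrollment". Partners appear separately: "Exploratory analyses will measure differences in the probability of initiating HCV treatment for HCV-infected partners by randomized group".

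The abstract says the data will be "analyzed using intention-to-treat and mixed-effects models". It mentions neither the risk ratio nor the survival framework.

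**The concern.** A dyad random intercept is useful when both members of a dyad contribute an outcome to the same model. For the trial's binary outcomes, the article points to one member only:

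- The primary comparison is by Index participants {20a}.
- Each Index participant enrols with a primary injecting partner {8}, and earlier participation in either role bars enrolment in the other {10}.
- The health-record request for initiation, completion and cure covers Index participants (Data sources, {18a}).

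That leaves one binary result per dyad. A logistic mixed model fitted to such data returns either a variance on the boundary or a variance set by the software's numerical settings, and the conditional odds ratio moves with it. A reader could then see an odds ratio well above the crude one, with nothing in the data to support the difference, next to the risk ratio from {20a}.

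**Working it through.** **Inputs.** Initiation 13% in control and 30% in intervention, 250 Index participants, 80% retention, 80% power, 5% level (Sample size {14}); 1:1 allocation (Trial design {8}), so 250/2 = 125 per arm. Assumed, because not stated: two-sided test, logit link, normal random intercept.

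**1. The plan's own figure.** For 13% v 30% with continuity correction, 102 per arm are needed, 204 in all, and 204/0.80 = 255 after attrition, against 250 stated. Exact (Fisher) power with 100 retained per arm is 80.0%. The stated size is reproduced closely and does not depend on any mixed model.

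**2. One binary outcome per dyad.** For dyad j in arm k, logit P(Y = 1 | u) = b_k + u_j, with u_j ~ N(0, s²). With one Y per dyad, the likelihood depends on (b_k, s) only through the marginal probability

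p_k = ∫ expit(b_k + s z) φ(z) dz.

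For any s, a b_k exists that gives p_k equal to the observed proportion. At that point

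log L = 125 × (0.13 ln 0.13 + 0.87 ln 0.87 + 0.30 ln 0.30 + 0.70 ln 0.70) = 125 × (-0.26523 - 0.12116 - 0.36119 - 0.24967) = -124.656,

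and s does not appear. At s = 0 the odds ratio is (0.30/0.70)/(0.13/0.87) = 2.87 and the risk ratio is 0.30/0.13 = 2.31. Solving for b_k at other values of s (80-point Gauss-Hermite quadrature):

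| SD of random intercept | Max. log-likelihood | Conditional OR | Marginal RR |
|---|---|---|---|
| 0 | -124.656 | 2.87 | 2.31 |
| 0.5 | -124.656 | 2.99 | 2.31 |
| 1 | -124.656 | 3.38 | 2.31 |
| 2 | -124.656 | 5.01 | 2.31 |
| 3 | -124.656 | 8.19 | 2.31 |
| 4 | -124.656 | 14.0 | 2.31 |

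The data cannot choose between these rows.

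**3. What changes if Partners are pooled in.** Let a share f of dyads also supply a Partner outcome. The article says only that some Partners will have untreated HCV, so f is taken over 0% to 100%. Further assumptions: true SD 1.5 and the same rates for Index and Partner. The expected drop in profile log-likelihood at SD 0, relative to SD 1.5, is:

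| f | Drop |
|---|---|
| 0% | 0 |
| 25% | 1.68 |
| 50% | 3.36 |
| 100% | 6.71 |

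The variance is therefore estimable in a pooled model, weakly when f is small.

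**The case against.** The strongest reply is that {20b} does not restrict the GLMM to Index participants. An intercept for dyad clustering makes sense if both members contribute, {20a} foresees initiation among HCV-infected Partners, and step 3 shows that pooling identifies the variance. This stands for a pooled model, but the article describes none. The Partner analysis is set out separately by randomised group, which is again one outcome per dyad. The intact-dyad extension in {20a} concerns continuous support variables. Pooling would also answer a different question from H1a.

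Second, no link is stated. Under a log link, the exponentiated treatment coefficient equals the marginal risk ratio whatever the variance, and under a logit link the risk ratio can be recovered by averaging over the random effect. Both points are correct. They limit the harm to a reported conditional odds ratio; they do not make the variance estimable.

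Third, a detailed analysis plan is still to come {20a} and could settle the link and analysis set. That is fair for those details. The random intercept itself, however, is stated in the article, with initiation as its example.

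Two stronger readings are tempting, and the text supports neither:

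- A reader might infer that the GLMM displaces the risk ratio. The primary comparison in {20a} is "cumulative incidence and risk ratios with 95% CI for HCV treatment initiation by Index participants", and the GLMM stands only under additional analyses. The abstract's line does not tie mixed models to the primary outcome.
- A reader might infer from "An exploratory linear mixed model (LMM) will assess the putative mechanisms of action" that a linear model is to be fitted to binary initiation. The wording is loose, but {20b} reserves linear mixed models for continuous outcomes, which largely resolves it.

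**Conclusion.** The point holds for Index-only binary outcomes. With one result per dyad there is no within-dyad clustering to model and the random-intercept variance is not identified. At the planned rates and under a logit link, the conditional odds ratio could be anything from about 2.9 (SD 0) to about 8 (SD 3) with the same fit, while the marginal risk ratio is 2.31 throughout.

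The reach is limited. The primary comparison and the sample size are unaffected. What is affected is the additional analysis in {20b} and the abstract's summary, which names mixed models without the risk ratio. The result rests on two assumptions: completion and SVR12, like initiation, are analysed in Index participants, as the health-record request indicates, and each outcome enters once per person. The range of odds ratios also requires the logit link.

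**What to change.** In {20b}:

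- Drop the dyad random intercept for Index-only binary outcomes and report a risk ratio from a model without it.
- For initiation, take that risk ratio from the survival framework in {20a}. A plain robust-variance Poisson model would ignore the censoring specified there.
- For completion and SVR12, standardised logistic regression or regression with robust standard errors would serve.
- Keep the dyad intercept, or GEE clustered on dyad, only for models that pool Index and HCV-infected Partner outcomes, and name that analysis set. If such a model is planned, note that the article describes a health-record request for Index participants only, so ascertainment may differ between the two roles.

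State that the {20a} risk ratio is the primary estimate, and bring the abstract into line. The cost is a few sentences and simpler code; no change to data collection or sample size is needed.

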### Methods in analysis to handle protocol non-adherence and any statistical methods to handle missing data {20c}

The primary analysis population will follow an intention-to-treat (ITT) approach, including all participants as originally assigned to their intervention groups regardless of adherence to the protocol. For protocol non-adherence, the analysis will use as-randomized analysis to maintain the validity of the randomized controlled trial design.

We will address incomplete data via direct maximum likelihood estimation (MLE) or multiple imputation (MI), which make the relatively mild assumption that incomplete data arise from a conditionally random (MAR) mechanism. Auxiliary variables will be included to help meet the MAR assumption and sensitivity analyses will be conducted with controlled MI to assess the robustness of the MAR assumption.

### Plans to give access to the full protocol, participant-level data and statistical code {31c}

The de-identified datasets analyzed during the current study and statistical code are available from the corresponding author on reasonable request, as is the full protocol. These plans are outlined in detail in our Data Sharing and Management Plan. We also plan to deposit the data and code in an open data repository, such as Zenodo or the Open Science Framework, following trial completion.”

### Oversight and monitoring

#### Composition of the coordinating center and trial steering committee {5d}

While this study does not include a formal Trial Steering Committee (TSC), oversight is ensured through regular meetings and structured processes involving the following groups:

Principal Investigator and Research Team: The PI and core team (clinical research coordinators, graduate student researchers, and data manager) provide day-to-day support. Responsibilities include participant recruitment, obtaining informed consent, intervention delivery, and data collection. The team also supports protocol development, study design and conduct, and manuscript preparation with guidance from the investigators. The team meets twice weekly with the PI to discuss trial operations and every 1–2 months to review progress, publications, and adherence to the protocol.

Community Academic Board (CAB): The CAB serves as the Stakeholder and Public Involvement Group (SPIG), composed of community representatives, patient advocates, and academic members. This board meets 6–12 times per year in person to provide input on recruitment strategies, community engagement, and dissemination plans.

Institutional Review Board (IRB): The IRB reviews the trial annually or as needed for protocol amendments, ensuring compliance with ethical and regulatory standards.

#### Composition of the data monitoring committee, its role and reporting structure {21a}

In accordance with the National Institutes of Health (NIH) and the primary funding agency, the National Institute on Drug Abuse (NIDA), we have developed a Data and Safety Monitoring (DSM) plan, and the PIs and core research team will maintain appropriate oversight and monitoring of the trial’s conduct in its entirety. As this trial is not a phase 3 trial and it was determined to be minimal risk to participants, no Data Safety Monitoring Board (DSMB) was required. The DSM plan was approved by the University of California, San Francisco Institutional Review Board (IRB) and NIDA before initiating enrollment.

#### Adverse event reporting and harms {22}

The primary risks to participants in the trial will be a breach of confidentiality and social stigma.

#### Frequency and plans for auditing trial conduct {23}

Trial conduct is monitored through internal audits conducted by the data manager on a weekly and monthly basis to ensure data quality, integrity, and adherence to the protocol. Findings are reported during biweekly operational meetings with the investigators and coordinating team. Issues occurring at the study site are reported immediately to the principal investigator and discussed during these regular meetings. Additionally, the principal investigator and coordinating team meet twice a year to specifically review the integrity of intervention delivery and adherence to the trial protocol.

#### Plans for communicating important protocol amendments to relevant parties (e.g. trial participants, ethical committees) {25}

Through March 21, 2024, three protocol amendments have occurred. Any future changes to the protocol will be reported to and approved by the UCSF Institutional Review Board (IRB) prior to implementation. Additionally, all amendments will be communicated to the study sponsor, the NIH, in accordance with reporting requirements outlined in the Data and Safety Monitoring Plan (DSMP). Any deviations from the protocol will be fully documented using a breach report form, which will be stored electronically and reviewed by the coordinating team. Major protocol breaches will be reported to the IRB within 5–10 days of the event occurrence or awareness, in accordance with UCSF IRB reporting requirements. The protocol will also be updated in the clinical trial registry (ClinicalTrials.gov) to reflect any changes.

#### Dissemination plans {31a}

The primary results of the trial will be reported in accordance with CONSORT guidelines, published in a peer-reviewed journal, and disseminated to the community via presentation at partnering community organizations and information sheet.

## Discussion

When complete, the YETI Partner Study will represent one of the first randomized clinical trials that evaluate the efficacy of an intervention to enhance partner support for starting HCV treatment. This trial will provide data on a new linkage intervention that can be integrated with existing HCV results disclosure counseling services, navigation services, and harm reduction services for PWID. If partner navigation yields at least a 20% increase in HCV treatment initiation, it could significantly impact public health strategies for addressing HCV among PWID.

Several practical and operational challenges are anticipated in performing the study. Ensuring participant engagement and retention is critical given the transient nature of the focal population and their complex social circumstances. Strategies such as providing transportation support, flexible scheduling, and regular follow-ups will be employed. Maintaining data quality and managing missing data will involve rigorous protocols, including double data entry, range checks, and using maximum likelihood and MI methods. Protecting participant confidentiality is paramount, with measures including the use of unique study ID numbers, secure data storage, and obtaining Certificates of Confidentiality.

Operational coordination with CBOs will be essential for participant recruitment and follow-up. Building strong relationships with CBOs and training their staff on study protocols and ethical considerations will be crucial. Ethical considerations, particularly obtaining informed consent and ensuring voluntary participation, will be carefully managed. The YETI Partner Study aims to address a critical gap in HCV treatment initiation among PWID by leveraging the supportive role of primary injecting partners, potentially informing future interventions and policies aimed at improving HCV treatment outcomes in marginalized populations.

### Trial status

Study protocol 1.4, 03/21/2024; recruitment began March 2024, estimated date recruitment is complete is December 2027.

## Data Availability

The data that support the findings of this study will be available from the corresponding author upon reasonable request. Access to the data will be granted following the approval of a Data Use Agreement to ensure the confidentiality and ethical use of the participant information.

## Abbreviations

PWID: People who inject drugs
HCV: Hepatitis C virus
DAA: Direct-acting antiviral
RCT: Randomized controlled trial
CBO: Community-based organization
SVR: Sustained virologic response
IDIP: Interpersonal factors underlying injection drug use
SPS-24: Source-Specific Social Provisions Scale
CESD: Center for Epidemiologic Studies Depression Scale
SU-SMS: Substance Use Stigma Mechanisms Scale
NIH: National Institutes of Health
NIDA: National Institute on Drug Abuse
IRB: Institutional Review Board
EMR: Electronic medical record
DSMB: Data Safety Monitoring Board
DSM: Data and Safety Monitoring
MRN: Medical record number
MI: Multiple imputation
LMM: Linear mixed model
GLMM: Generalized linear mixed model
MAR: Missing at random
SPIRIT: Standard Protocol Items: Recommendations for Interventional Trials
REDCap: Research Electronic Data Capture
CONSORT: Consolidated Standards of Reporting Trials
